### Data analysis

Data analysis, processing and calculation of inferential statistics will be performed primarily using SPSS software. In relation to primary endpoint analysis, which assesses the presence of SSI within 30 days following reversal surgeries, a Chi-squared test will be used to compare the SSI incidence rates between the two randomized groups (PREVENA vs conventional surgical dressings). The time to wound healing, patient experience and satisfaction and the degree of wound healing and wound aesthetics will be presented as secondary outcomes. A t-Test will be applied to compare the time to wound healing between the randomized groups as appropriate. Similarly, t-Test will be applied to compare the level of satisfaction between patients of the randomized groups. All outcome measures will be presented with 95% confidence intervals and two-sided test *p* values.

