### Interventions

Following selection and attainment of informed consent, all participants will be randomly assigned to either the PREVENA therapy group or conventional dressings group with a 1:1 allocation ratio via stratified randomisation. Participants will be stratified by their baseline comorbidity state and will be stratified into one of the three groups, namely:i)No diabetes nor immunosuppressant useii)Diabetic patients (both insulin, non-insulin dependent, type one or type two)iii)Use of immunosuppressants

Following stratification, participants will be systematically randomized in a 1:1 allocation ratio into either the PREVENA group or the conventional dressing group. The conventional dressings that are used in the study will be non-antimicrobial, standard surgical dressing. On the day of elective admission, the relevant primary or co-investigators will perform this randomisation by picking one of the sealed envelopes containing the assignment. There will be equal proportion of assignments to either group (PREVENA and conventional dressings) to achieve a 1:1 allocation ratio. The conventional dressings that are used in the study will be non-antimicrobial, standard adherent surgical dressing. Due to the nature of the intervention, neither the participants nor the staff can be blinded to allocation. Prophylactic antibiotics will be administered following reversal surgeries as per local guidelines. Initial dose will be administered during induction of the surgeries, followed by three more doses administered post-operatively. Wound closure will be performed in a standardized manner, and the randomized dressing will be applied immediately after wound closure. The PREVENA dressings will be left in situ for 7 days at which point the wound will be inspected for any evidence of SSI. Wound swabs will be performed for culture and sensitivity for any incidence or suspicion of SSI.

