### Sample size

Based on published literature, we hypothesize a 60% reduction in SSI rates following the routine use of NPWT (25 to 10% at closure site). The study will be a randomized, controlled, open-label trial with two parallel arms comparing standard and routine NPWT applied immediately after reversal of ileostomy or colostomy. The sample size required to achieve a power of 1-β = 0.80 and at the level α = 0.05 under these assumptions (including a margin error with application failure, saturation and patient non-compliance) amounts to 100 patients needed for each arm; thus 2 × 100 = 200 participants are required. We incorporate a 10% dropout rate in our sample size calculation, and this would inflate the sample size to approximately 222 participants.

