### Subgroup analysis

We intend to conduct a subgroup analysis given the strong biological rationale and potential interaction effects these variables may have on measured outcomes. These variables include age, presence of co-morbidities such as diabetes mellitus and the use of immunosuppressants which may impair the process of wound healing.

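### The primary chi-squared test leaves out the comorbidity strata used in randomisation, and two of those strata overlap: a minor point with a cost-free improvement

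*Protocol article*

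**What the plan says.** All four places are in the protocol article.

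- **Interventions** sets up stratified 1:1 randomisation: "Participants will be stratified by their baseline comorbidity state and will be stratified into one of the three groups". The first group has neither diabetes nor immunosuppressant use. The other two are listed as "Diabetic patients (both insulin, non-insulin dependent, type one or type two)iii)Use of immunosuppressants". On the day of admission an investigator draws a sealed envelope. Separate envelope sets or blocks for each stratum are not described.
- **Subgroup analysis** gives the reason these factors matter, naming the "presence of co-morbidities such as diabetes mellitus and the use of immunosuppressants which may impair the process of wound healing".
- **Data analysis** fixes the primary test: "a Chi-squared test will be used to compare the SSI incidence rates between the two randomized groups". It adds: "All outcome measures will be presented with 95% confidence intervals and two-sided test" p values. No stratum term appears.
- **Sample size** assumes SSI rates of 25% and 10%, "at the level α = 0.05 under these assumptions", with 80% power, and arrives at 100 per arm and about 222 in total after 10% dropout.

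**The concern.** Stratifying on a prognostic factor removes part of the chance variation between arms. A test that ignores the strata still counts that variation in its variance. Its standard error is then too large, its p value a little too big and its confidence interval a little too wide. The protocol itself expects these factors to affect healing, so the design and the primary analysis do not match. At stake is a modest amount of precision that the design has already paid for.

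The second issue is one of definition. Each participant is to go into one of three groups, but a diabetic patient taking immunosuppressants meets the description of two. A stratified analysis needs a stratum that is defined in the same way for everyone.

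**Working it through.** **1. The plan's own figure.** Inputs from Sample size: 25% and 10%, α = 0.05 (two-sided, from Data analysis), power 0.80. The mean rate is (0.25 + 0.10)/2 = 0.175. With the pooled-variance formula for two proportions,

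n = [1.960 × √(2 × 0.175 × 0.825) + 0.842 × √(0.25 × 0.75 + 0.10 × 0.90)]² / 0.15² = 99.5, so 100 per arm.

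This matches the plan, with formula power 80.2% at 100 per arm. Dropout: 200/0.9 = 222.2, also a match. The trial is therefore sized for the unstratified test that it names.

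**2. Why ignoring the strata is conservative.** With stratum shares w and rates p, the variance in the plain test splits into two parts:

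p̄(1 − p̄) = Σ w p(1 − p) + Σ w (p − p̄)².

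If arms are balanced within strata, the second part does not contribute to the true variance of the difference. Example with assumed shares 75/15/10%, odds ratio 3 for both risk strata and no treatment effect. The rates are 19.37% and 41.89%, averaging 25%.

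- Within strata: 0.75 × 0.1937 × 0.8063 + 0.25 × 0.4189 × 0.5811 = 0.1780.
- Total: 0.25 × 0.75 = 0.1875.
- Ratio of standard errors: √(0.1875/0.1780) = 1.026.
- The effective critical value is 1.960 × 1.026 = 2.01, a two-sided error of about 4.4%.

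**3. Simulation.** The documents give no stratum shares or effects, so these are assumptions. Settings: 200 patients, balance within strata, control rate 25%, and a common treatment odds ratio set so that the NPWT rate averages 10% (or equals 1 for the null). There were 100,000 runs per row. The Cochran-Mantel-Haenszel (CMH) statistic sums x₁ − n₁m/n over strata and divides by the root of the summed n₁n₀m(n − m)/[n²(n − 1)]. Here x₁ is NPWT events, m all events, n₁ and n₀ the arm sizes and n the stratum size. Shares 75/15/10%:

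| Stratum odds ratio | Type I error, chi-squared | Type I error, CMH | Power, chi-squared | Power, CMH | Mean unstratified SE | True SD of the difference |
|---|---|---|---|---|---|---|
| 1 | 5.0% | 5.0% | 81.5% | 81.2% | 0.0523 | 0.0525 |
| 2 | 4.8% | 5.0% | 81.6% | 81.8% | 0.0523 | 0.0523 |
| 3 | 4.4% | 5.0% | 82.1% | 82.8% | 0.0523 | 0.0516 |
| 5 | 3.8% | 5.0% | 82.5% | 84.4% | 0.0523 | 0.0504 |

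The standard errors are at 25% versus 10%. The overstatement is 0.0523/0.0523 = 1.00 at odds ratio 2, 0.0523/0.0516 = 1.01 at 3 and 0.0523/0.0504 = 1.04 at 5. With shares 60/25/15%, power is within about 0.3 points of these values, and chi-squared type I error is 4.6%, 4.4% and 3.7% at odds ratios 2, 3 and 5.

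**4. Unequal risk strata.** Assumed shares 70/20/10%, 200,000 runs:

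| Control rates by stratum | Odds ratios against stratum i | Type I error, chi-squared vs CMH | Power, chi-squared vs CMH |
|---|---|---|---|
| 20/35/40% | 2.2 and 2.7 | 4.6% vs 4.9% | 81.8% vs 82.2% |
| 17/40/51% | 3.3 and 5.1 | 4.1% vs 5.0% | 82.2% vs 83.8% |
| 12/50/66% | 7.3 and 14.2 | 2.7% vs 5.0% | 83.7% vs 87.9% |

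The odds ratios follow from the rates; for example, (0.35/0.65)/(0.20/0.80) = 2.2. The last row is an extreme bound, not a planning scenario.

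**5. The overlap.** Stratum ii covers every type of diabetes and does not exclude immunosuppressant users. Stratum iii covers immunosuppressant use and does not exclude diabetics. A patient with both fits ii and iii, and the text gives no priority. No arithmetic is needed.

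**The case against.** The case for leaving the plan alone is strong on size. The chi-squared test is valid after stratified randomisation and does not inflate type I error. The sample size was computed for that same test, and its power exceeds 80% in every scenario. At stratum odds ratios up to 2 the power loss is negligible. The conservatism also requires real balance within strata. Interventions describes an envelope draw with equal overall proportions and nothing specific to a stratum. If the draw does not balance the strata, the unadjusted interval is not over-wide, although adjustment could still gain some precision. Finally, this is a condensed article, and a tie-break rule or a supporting adjusted analysis may stand in a fuller document. All of this holds, and it is why the point is minor. What remains is that the article does name the primary test and does define the strata, and the two do not fit together.

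A reader might infer more than the text supports:

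- *The trial is underpowered or its result invalid.* The calculations show neither.
- *An investigator could choose the stratum and so the envelope set.* The article describes no stratum-specific sets. Even with them, allocation would be biased only if the next assignment were predictable, which nothing here shows.
- *The overlap spoils the subgroup analyses.* The subgroup section lists diabetes and immunosuppressant use separately, so each can be analysed as yes or no whatever stratum was assigned.
- *Site should be added as a covariate.* Site is not a stratification factor in Interventions, so this does not follow from the argument, and a CMH test takes no covariates.

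**Conclusion.** The point holds as a minor matter of efficiency and consistency; it is not an error of validity. If the strata are prognostic and balanced by the draw, the stated test runs at about 4.5% type I error for stratum odds ratios of about 2 to 3 and about 4% for 3 to 5. It gives up about 0 to 2 points of power, and at the planned rates its standard error is too large by about 0 to 4%. These sizes rest on assumed stratum shares and effects. The 4-point loss in the most extreme scenario needs odds ratios of about 7 and 14 and should not be cited as the expected cost. The overlap of strata ii and iii rests on the text alone and needs no assumption.

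**What to change.** - In Data analysis, make the primary test a Cochran-Mantel-Haenszel test by the randomisation strata, or a logistic regression with a stratum term. Report the stratum-adjusted risk difference with 95% CI, and keep the plain chi-squared test as a sensitivity analysis.
- Use a variance formula suited to small strata for that interval. In the simulation with 75/15/10% shares and odds ratio 2, the simple plug-in stratified standard error averaged 0.0512 against a true 0.0523, about 2% too small.
- In Interventions, make the strata mutually exclusive, for example: none / diabetes without immunosuppressants / any immunosuppressants. Another grouping would serve if it places every patient once. If patients have already been randomised, use the stratum recorded at randomisation.

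The cost is a revised analysis statement and one line in the randomisation procedure, with no new data and no change in sample size. If the strata turn out not to be prognostic, the stratified test costs at most about 0.3 points of power in these simulations (81.5% against 81.2%).

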### Subgroup analysis

We intend to conduct a subgroup analysis given the strong biological rationale and potential interaction effects these variables may have on measured outcomes. These variables include age, presence of co-morbidities such as diabetes mellitus and the use of immunosuppressants which may impair the process of wound healing.

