### Inclusion criteria

PRIC Study will include patients who are electively admitted to St. James’s Hospital or Tallaght University Hospital for reversal of loop ileostomy or colostomy. Patients must be 16 years of age or older and consent to the follow-up protocols.

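### The primary chi-squared test is valid but makes no use of age; pre-specifying age as a covariate could add a little precision at almost no cost

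*Protocol article*

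**What the plan says.** All references are to the protocol article.

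- **Data analysis:** for the primary endpoint, "a Chi-squared test will be used to compare the SSI incidence rates between the two randomized groups". No covariate is mentioned.
- **Subgroup analysis:** "These variables include age, presence of co-morbidities such as diabetes mellitus", followed by immunosuppressant use, with impaired wound healing as the mechanism. The reason given is the "strong biological rationale and potential interaction effects these variables may have on measured outcomes".
- **Interventions:** "Participants will be stratified by their baseline comorbidity state". The three strata are neither condition, diabetes, and immunosuppressant use. Age is not among them.
- **Inclusion criteria:** "Patients must be 16 years of age or older and consent to the follow-up protocols". Age must therefore be known for every participant. The article does not say in words that age is recorded for analysis; this is inferred from the eligibility check and the planned age subgroup.
- **Sample size:** SSI rates of "25 to 10% at closure site", with "power of 1-β = 0.80 and at the level α = 0.05", lead to 100 per arm.

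**The concern.** Age is singled out as a variable that may matter for the outcomes, and it will be at hand for everyone. Its only planned use is to split the sample into subgroups. With 25 + 10 = 35 expected events, that is where the trial can learn least. The main comparison, where a prognostic covariate could sharpen the estimate, leaves it out. Adjusting for the three strata would recover age only to the extent that age is correlated with diabetes or immunosuppressant use.

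At stake is a little power. The stated 100 per arm is what the plain two-proportion formula gives with nothing added, so there is no slack in that number. There is also a practical benefit. In an open-label trial, a covariate fixed in advance removes any temptation to decide on adjustment after seeing an age imbalance.

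**Working it through.** **1. Reproduce the stated sample size.** Inputs from the Sample size section are 25% v 10%, α = 0.05 and power 0.80; two-sided testing comes from Data analysis. With pooled rate (0.25 + 0.10)/2 = 0.175:

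n = [1.960·√(2 × 0.175 × 0.825) + 0.842·√(0.25 × 0.75 + 0.10 × 0.90)]² / 0.15²

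= [1.960 × 0.5374 + 0.842 × 0.5268]² / 0.0225 ≈ 99.5, rounded up to **100 per arm**.

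Power at 100 per arm is 0.802. The stated figure matches an unadjusted comparison exactly, so the plan's test and sample size agree.

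**2. What adjustment for age would add.** The documents give no age–SSI association, so its strength is an assumption, expressed as an odds ratio per SD of age and shown over a range. Simulation used 100 per arm, standard normal age with a log-linear effect, marginal rates held at 25% and 10%, and 8,000 trials per setting. The Pearson chi-squared test is compared with the likelihood-ratio test of arm from a logistic model with age. The variance ratio is that of the age-standardised risk difference to the crude one. Type I error is taken at 25% v 25%.

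| Assumed odds ratio per SD | Power, chi-squared | Power, with age | Gain (points) | Variance ratio | Type I error, chi-squared / with age |
|---|---|---|---|---|---|
| 1.0 | 81.7% | 81.6% | −0.1 | 1.01 | 5.1% / 5.5% |
| 1.25 | 81.8% | 82.1% | 0.3 | 1.00 | 5.0% / 5.2% |
| 1.5 | 81.1% | 82.1% | 1.0 | 0.98 | 5.3% / 5.7% |
| 2.0 | 81.5% | 83.5% | 2.0 | 0.95 | 5.1% / 5.2% |
| 2.5 | 81.6% | 85.8% | 4.2 | 0.90 | 5.4% / 5.7% |

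Simulated chi-squared power lies slightly above the formula's 80.2%; the differences within rows are what matter. Further runs of the same design gave gains of 0.4 to 0.5 points at an odds ratio of 1.3, 0.8 to 1.0 at 1.5, and 2.0 to 3.0 at 2.0. The variance ratio at 1.3 was 0.99. For 1.3 to 2.0 the gain is therefore about 0.4 to 3 power points, with 1 to 5% lower variance.

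**3. Chance imbalance in age.** The standardised difference in mean age between arms has SD √(2/100) = 0.14. In simulation the crude risk difference moved by 0.043 to 0.094 per SD of age difference (odds ratios 1.3 to 2.0). A one-standard-error imbalance therefore shifts it by 0.043 × 0.141 = 0.006 to 0.094 × 0.141 = 0.013, that is 0.6 to 1.3 percentage points. The standard error of the risk difference is √[(0.25 × 0.75 + 0.10 × 0.90)/100] = 0.053, or 5.3 points. The shift is thus roughly 0.1 to 0.25 of a standard error.

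**The case against.** The case against raising this has real force.

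- **The chosen test is not wrong.** A chi-squared test of two randomised proportions is valid, keeps its type I error near 5% whether or not age matters, and fits the stated sample size. This stands in full. A reader might infer that the primary comparison is biased because an age imbalance goes unadjusted. The documents do not support that: chance imbalance under randomisation is random error already covered by the confidence interval and p value.
- **The protocol does not say that age predicts SSI.** A reader might infer it from the Subgroup analysis section. That section argues from interaction, and the mechanism it names is impaired wound healing, which is a secondary outcome. Its mention of measured outcomes could include SSI, but it gives no direction or strength. Precision may be lost; it is not shown to be lost.
- **The gain is small and rests on assumed odds ratios.** Up to 1.5 per SD it is about one point or less. The adjusted likelihood-ratio test also ran slightly above the chi-squared test in type I error (5.2 to 5.7% v 5.0 to 5.4%), so part of the smallest gains may reflect the choice of test. This stands and limits the claim.
- **An article condenses, and an adjusted analysis may sit in a fuller document.** A supporting analysis may well. The primary test, however, is fixed in the article itself, so it is fair to comment on that choice.
- **The stronger case for adjustment concerns the stratification factors**, which the primary test also ignores. That is so, and age fits naturally into the same model.

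**Conclusion.** The point holds as a modest efficiency improvement. The primary test is valid and consistent with 100 per arm, but it leaves unused a baseline variable that the protocol itself considers relevant and should have for every patient. If age predicts SSI with an odds ratio between 1.3 and 2.0 per SD, adjustment brings about 0.4 to 3 points of power and a 1 to 5% reduction in the variance of the risk difference. If age is unrelated to SSI, the change is essentially nil.

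These figures rest on the assumed odds ratios, a log-linear age effect, the planned rates of 25% and 10%, and 100 analysed patients per arm. Nothing here shows that the planned analysis is invalid, biased or underpowered. Leaving the plan as it is would be defensible.

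**What to change.** In the Data analysis section, pre-specify the primary model as a logistic regression of 30-day SSI on arm, age as a continuous variable, and the randomisation stratum. Report the standardised (marginal) risk difference with its 95% confidence interval, and keep the Pearson chi-squared test as a supporting analysis. Fix this before any comparison by arm is seen, including the month-6 interim analysis, which looks at SSI in the two groups. Check the type I error of the chosen adjusted test by simulation at the planned size.

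The cost is a sentence or two of text and a few lines of code, with no new data if age is recorded as inferred above. The model has four terms besides the intercept (arm, age and two for the strata) on about 35 expected events, or 35/4 ≈ 9 events per term, which is workable. The one small downside is that the primary estimate becomes model-based.

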### Data monitoring

An interim analysis will be conducted at month 6 to assess recruitment, the overall SSI rate between two groups and the failure of protocol rates. The PRIC Study may potentially be expanded internationally and conducted at other clinical facilities. The data monitoring process and interim analysis will be carried out independently from any third parties and any potential sponsors.

## Discussion

At present, there is a lack of consensus on the routine use of NPWT in the setting of stoma reversal. To date, there have been four randomized trials that have investigated the use of NPWT in stoma reversal, and the results from these studies are conflicting and inconclusive. The NEPTUNE trial observed that the prophylactic use of NPWT was not associated with a decrease in 30-day SSI incidence rate when compared to standard dressings, with the 30-day SSI incidence of the NPWT group being 32% versus 34% in the standard dressing group [17]. Uchino et al. also noted no difference in the efficacy rates between the use of NPWT and purse-string suture methods in preventing SSI [21]. Similarly, Carrano et al. reported similar incidence rates of SSI and wound complications in both the NPWT and conventional dressing cohorts [22]. In contrast, the trial conducted by Wierdak et al. reported a positive benefit in the use of prophylactic NPWT in the setting of ileostomy closure, with a reduced incidence of SSI and wound healing complications. They had a SSI incidence of 5.7% in the NPWT group versus 22.2% in the standard dressing cohort [23]. Similarly, wound healing complications, defined as any condition of the wound that required post-operative intervention other than a change of dressing or removal of stiches, were significantly lower in the NPWT group (8.6% versus 30.6%) [23]. In addition to these conflicting results, these studies are not sufficiently powered, thereby supporting the need for further evaluation and support the relevance of PRIC Study in establishing whether the routine use of NPWT does reduce SSI rate when compared to using conventional dressings.

In addition, current literature lacks research studies that employ microbiology wound swabs and culture in their assessment of SSI. PRIC Study will involve the use of microbiology wound swab, culture and sensitivity to help improve the accuracy of assessing and reporting SSI incidence. And to our knowledge, the PRIC Study is the first study that employs microbiological wound swabs in assessing SSI in the setting of reversal of ileostomy and colostomy surgeries.

In relation to the indirect or non-medical standpoint, the financial costs associated with the incidence of SSI are substantial. SSI is thought to contribute to twice as much as the inpatient costs than a patient without SSI [24]. They contribute to an increased financial burden via prolonged hospitalization, reoperation/intervention and/or readmission [4]. The PRIC Study will assess not only the incidence of SSI, but also the time required to wound healing, and these results may be used to inform future cost–benefit analytical studies.

Although the purse-string closure technique has been reported to have considerable success in reducing the rate of SSI incidence [5, 6], there are concerns pertaining to this method primarily due to the slow time to complete wound healing and unsatisfactory wound aesthetics [25]. The PRIC Study will also evaluate whether the use of PREVENA Therapy leads to better wound healing and appearance as compared to conventional dressings. Whilst it is crucial that we continue to seek better strategies to reduce the incidence of SSI and other associated post-operative complications, it is equally important that we do not neglect the psychological aspects and patients’ experience with any proposed interventions. Stoma reversals are known to incur prolonged social and psychological impacts on patients [26] despite their low mortality rates of less than 4% [27]. Following stoma reversals, patients are at risk of developing post-operative complications such as small bowel obstruction, SSI, parastomal hernia, anastomotic leak and enterocutaneous fistulae [28] and often have to cope with significant alteration in bowel function which greatly affects daily routines [29]. The PRIC Study will assess the patient experience with their application of PREVENA Therapy and will address the concerns and reservations associated with the use of PREVENA Therapy.
[figure not shown]
